### Data collection and management

3.2

#### Data collection

3.2.1

To ensure data accuracy and integrity, a dedicated research coordinator will be responsible for collecting all assessment data. Standardized Case Report Forms (CRFs) will be designed, and a dedicated electronic database will be established to systematically record patient demographics, treatment details, and all outcome measures.

#### Statistical analysis

3.2.2

Data will be analyzed using SPSS software (version 26.0, IBM Corp., Armonk, NY, USA). Continuous variables will be presented as mean ± SD, and categorical variables as frequency (n) and percentage (%). The primary outcome is the change in VAS score from baseline to 6 weeks, and an independent samples *t*-test will be used to compare the change scores between the two groups. For outcomes measured at multiple time points (baseline, 6 weeks, 6 months, and 3 years), a linear mixed-effects model will be employed to account for within-subject correlations and to handle missing data under the missing at random assumption, including group, time, and group-by-time interaction as fixed effects and subjects as random effects.

As this is a non-randomized study, baseline characteristics (including age, sex, body mass index, and baseline VAS score) will be compared between groups, and if any significant imbalance is detected, these variables will be included as covariates in the primary analysis to adjust for potential confounding. Secondary outcomes will be analyzed using independent samples *t*-tests for continuous variables and chi-square tests for categorical variables. Missing data will be handled using multiple imputation for sensitivity analysis. A two-tailed *P*-value < 0.05 will be considered statistically significant for all analyses.

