### Sample size

2.6

The sample size for this study was determined through an *a priori* power analysis based on a two-independent-sample means comparison, aimed at detecting differences in the change scores (pre- to post-intervention) of the primary continuous outcome (VAS) between the two groups. Based on previous studies or pilot data, we assumed a mean difference of *δ* = 1.1*σ* between the groups, with an estimated population standard deviation of *σ* = 2.0. The significance level was set at *α* = 0.05 (two-tailed) and the statistical power (1–*β*) at 0.95. Using the corresponding formula (1), a sample size of 43 participants per group was calculated, resulting in a total of 86 participants.$$n_{1}=n_{2}=2{\left(\frac{z_{\alpha /2}+z_{\beta }}{\delta /\sigma }\right)}^{2}$$

To account for potential loss to follow-up or dropouts and to ensure reliable between-group comparisons and data analysis in a real-world setting, the sample size was increased by approximately 10%. Thus, a total of *n* = 96 participants with patellofemoral pain syndrome are planned to be recruited, with *n* = 48 in each group. All eligible patients will be consecutively assessed for eligibility during the study period and assigned to the corresponding intervention group.

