#### Primary outcome

3.1.1

The primary outcome is pain intensity measured using a 0–10 Visual Analog Scale (VAS), where 0 represents no pain and 10 represents the worst possible pain. The change in VAS score from baseline to each follow-up time point (6 weeks, 6 months, and 3 years) will be used as the primary endpoint.

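### As written, the mixed model gives all four visits one variance and one correlation; if correlation fades with time, the 3-year contrast gets too small a standard error

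*Protocol article*

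**What the plan says.** Section 3.2.2 (Statistical analysis) contains two analyses that bear on VAS.

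- For the change to 6 weeks, which this section calls the primary outcome, "an independent samples *t*-test will be used to compare the change scores between the two groups".
- For outcomes assessed at baseline and again at the 6-week, 6-month and 3-year visits, the plan is this: "a linear mixed-effects model will be employed to account for within-subject correlations and to handle missing data under the missing at random assumption". The model has terms for treatment group and for visit, and beyond those it takes the "group-by-time interaction as fixed effects and subjects as random effects".

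The section names no random slope, residual covariance structure, robust standard error or degrees-of-freedom method.

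Section 3.1.1 (Primary outcome) casts the primary endpoint more widely: "The change in VAS score from baseline to each follow-up time point (6 weeks, 6 months, and 3 years) will be used as the primary" one. The mixed model is the only analysis that section 3.2.2 gives for VAS at 6 months and 3 years. It therefore serves time points that section 3.1.1 counts as primary. The significance rule is uniform: "A two-tailed *P*-value < 0.05 will be considered statistically significant for all analyses".

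**The concern.** A random subject effect with ordinary independent residuals implies compound symmetry: equal variance at each visit and the same correlation between any two visits. Here the gaps between visits run from 6 weeks to 3 years. Pain scores taken 6 weeks apart will usually correlate more closely than scores taken 3 years apart, and the spread of scores may change after treatment.

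The model pools all of this into one within-subject variance, so every change-from-baseline contrast between groups gets the same standard error when data are complete. If the true variance of the change to 3 years exceeds the pooled value, the confidence interval at 3 years is too narrow and false positives are too frequent.

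The model is also the stated means of handling missing data under missing at random. That use of a likelihood model relies on the covariance being right, and the reliance is heaviest where dropout is likely to be greatest. That second effect has not been quantified here.

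**Working it through.** **Inputs.** From the protocol (section 2.6): SD 2.0, 43 per group before dropout, two-sided alpha 0.05. From section 3.2.2: the model terms and the four visits. Assumed, because the protocol gives none: all correlations between visits and any SD that differs by visit.

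The protocol has no figure of its own for this standard error, so there is none to reproduce. The 43 per group is taken as stated. The formula printed in section 2.6 does not in fact return it (2 × ((1.960 + 1.645)/1.1)² = 21.48, so 22 per group). That is a separate matter, and n cancels from the ratios below.

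**Formulas (complete data, n per group).** Write V for the true 4 × 4 covariance matrix, with baseline as visit 0.

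- Variance of a change, as the model sees it: 2 × (mean of the four variances − mean of the six covariances), the same for every follow-up visit.
- True variance of the change to visit k: V00 + Vkk − 2·V0k.
- SE of the between-group contrast: √((2/n) × variance of change).
- Ratio r = model SE / true SE. Actual two-sided type I error ≈ 2 × (1 − Φ(1.96 r)).

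**Worked case, stronger decay.** Equal SDs of 2.0; correlations with baseline 0.6, 0.4, 0.2; among follow-ups 0.5 (6 weeks–6 months), 0.3 (6 weeks–3 years), 0.4 (6 months–3 years).

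- Mean correlation: (0.6 + 0.4 + 0.2 + 0.5 + 0.3 + 0.4)/6 = 0.4.
- Model variance of change: 2 × 4 × (1 − 0.4) = 4.8 at each visit; SE = √((2/43) × 4.8) = 0.47.
- True variance at 6 weeks: 2 × 4 × (1 − 0.6) = 3.2; SE 0.39; r = √(4.8/3.2) = 1.22; type I error 1.6%.
- True variance at 6 months: 2 × 4 × (1 − 0.4) = 4.8; SE 0.47; r = 1.00; type I error 5.0%.
- True variance at 3 years: 2 × 4 × (1 − 0.2) = 6.4; SE 0.55; r = √(4.8/6.4) = 0.87; type I error 9.0%.

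A simulation of 20,000 complete trials with 43 per group agrees: 1.7%, 5.1% and 8.7%.

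**Other covariance patterns.** Correlations are listed as with baseline; among follow-ups in the order above.

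| Assumed pattern | r at 6 weeks | r at 3 years | Type I error at 3 years |
|---|---|---|---|
| Constant correlation, equal SDs | 1.00 | 1.00 | 5% |
| Milder decay (0.5, 0.4, 0.3; 0.5, 0.4, 0.5), equal SDs | 1.06 | 0.90 | 8% |
| Stronger decay (worked case) | 1.22 | 0.87 | 9% |
| Baseline weakly related to follow-ups (0.3, 0.25, 0.2; 0.6, 0.5, 0.6), equal SDs | 0.92 | 0.86 | 9% |
| Decay (0.6, 0.5, 0.3; 0.65, 0.4, 0.5), SDs 1.5, 1.8, 2.0, 2.4 | 1.35 | 0.83 | 10% |
| Same decay, SDs 2.2, 1.8, 1.7, 1.6 | 1.03 | 0.81 | 11% |
| Same decay, SDs 2.4, 2.0, 1.5, 1.3 | 0.96 | 0.81 | 11% |

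The 3-year standard error is too small in every non-constant pattern tried. The 6-week standard error is too large in some, about right in one and too small in others.

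**The case against.** The strongest reply is that the article does not say subject is the sole random term, and it does not say the residuals are independent. SPSS mixed models can carry a structured residual, and covariance structure is often left to an analysis plan. That much stands: compound symmetry is how the printed text reads, not something it declares. But the article does more than stay silent. It lists the model's terms one by one, and an analyst who followed that list would fit a random intercept. The point is therefore about a stated model that suits the visit schedule badly, not about a missing detail.

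The second reply is that the 6-week comparison, on which the sample size rests, is a t-test on change scores. It uses the observed variance of those changes, and the mixed-model covariance does not enter it. That is correct, and it confines the point to the mixed-model results.

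The third reply is that every figure rests on assumed correlations. This also stands. The figures show what can happen; they do not predict what will.

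A reader might go further and infer that the 6-week and 3-year standard errors are wrong in opposite directions. The documents do not support that. It follows from decaying correlation with roughly stable SDs, but the table shows patterns in which both errors have the same sign, and one in which the 6-week error nearly vanishes.

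**Conclusion.** The point holds for the mixed-model inference at the later visits. Read as written, section 3.2.2 ties all four visits to one variance and one correlation. If within-subject correlation decays over time, the standard error at 3 years is too small: in the decay patterns examined it is about 10% to 19% below the true value, for a type I error of about 8% to 11% in place of 5%. If correlation and variance are constant, nothing is wrong. At 6 months the error is smaller and can go either way. These figures assume complete data.

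The 3-year result matters because section 3.1.1 places it within the primary endpoint and section 3.2.2 offers no other analysis of it. No conclusion should be drawn that the 6-week primary test is miscalibrated.

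**What to change.** In section 3.2.2, replace the random subject effect with a repeated-measures mixed model: group, time and group-by-time as fixed effects, an unstructured within-subject covariance across the four visits, and Satterthwaite degrees of freedom (or Kenward-Roger if the software supports it). The unstructured matrix should replace the random intercept and not be added to it, since it already contains whatever the intercept would describe.

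Name a fallback for non-convergence, such as heterogeneous Toeplitz, or compound symmetry with robust standard errors. Robust errors would repair the intervals but would not remove the reliance of the missing-data handling on the covariance model, so they are better placed last.

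The cost is wording only, with no extra data. The structure has 4 variances and 6 covariances, 10 parameters in all, which 96 patients at four visits can support. It covers every pattern in the table, so the sponsor need not know in advance which is true. The one downside is a small chance of non-convergence, which the fallback covers. The change can be made before the June 2026 start given in section 2.2.

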## Introduction

1

Patellofemoral pain syndrome (PFPS) is the most prevalent chronic knee disorder among adolescents and adults, characterized primarily by peripatellar or retropatellar pain during patellofemoral joint loading activities (e.g., squatting, stair ambulation, and running) (1–6). Evidence indicates that about 80% of individuals with PFP continue to have pain despite completing rehabilitation programs (7). Patellofemoral pain syndrome represents a major socioeconomic burden, evidenced by musculoskeletal disorder costs of £7.4 billion per year in the UK and over $213 billion in the US (5). Therefore, this disease presents a critical clinical challenge, driven by the convergence of high prevalence, suboptimal long-term outcomes and significant economic costs that highlight the pressing need for objective diagnostic tools.

It has been established in the literature that the diagnosis of patellofemoral pain is challenging, partly due to the absence of a clear gold-standard reference test (8, 9). Within the domain of medical imaging, a key limitation is that static imaging cannot adequately assess dynamic patellar function, as it provides only a snapshot of non-physiologic joint position (10). Consequently, clinical decision-making becomes disconnected from the core pathomechanism, resulting in imprecise diagnosis, non-targeted therapy, and unstable therapeutic outcomes.

To address these challenges, it is imperative to shift the focus toward dynamic biomechanical assessment. This approach directly targets the core issue by quantifying patellofemoral joint function during activity, thereby bridging the critical gap left by conventional subjective evaluation and static imaging.

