#### Inclusion criteria

2.4.1

To be eligible, individuals must (1) be 40 to 60 years of age; The age range of 40–60 years was selected based on a 10-year review of hospital medical records showing that PFPS patients in our setting are predominantly concentrated in this age group. (2) fulfill the clinical diagnostic criteria for patellofemoral pain syndrome (PFPS), including anterior knee pain exacerbated by functional activities (e.g., stair negotiation, squatting), with imaging (x-ray or MRI) confirming no other knee pathologies; and (3) provide written informed consent.

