#### Exclusion criteria

2.4.2

Individuals will be excluded if they have (1) significant systemic disease (e.g., cardiovascular, pulmonary, hepatic, renal, or psychiatric) that could confound assessment or outcomes; (2) concomitant major knee joint pathology such as fractures, ligamentous ruptures, rheumatoid arthritis, or gouty arthritis; or (3) undergone any recent surgical procedure or targeted therapy for the patellofemoral joint. (4) radiographic evidence of knee osteoarthritis with Kellgren-Lawrence grade≥2.

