### Group allocation and intervention

2.5

Patients will be assigned to either the experimental group or the control group based on their preference after receiving standardized information about both interventions. Specifically, the experimental group will receive biomechanical monitoring, targeted exercise, and Traditional Chinese Medicine (TCM), whereas the control group will receive conventional exercise and the same TCM regimen as the experimental group.

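### Patients choose their arm, yet symptom duration and earlier rehabilitation of the study knee are not shown to be recorded or adjusted for in the VAS comparison

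*Protocol article*

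**What the plan says.** Allocation is not randomised. Under Group allocation and intervention: "Patients will be assigned to either the experimental group or the control group based on their preference after receiving standardized information about both interventions".

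The Statistical analysis section acknowledges this and states that "baseline characteristics (including age, sex, body mass index, and baseline VAS score) will be compared between groups". The rule for using them is conditional: "if any significant imbalance is detected, these variables will be included as covariates in the primary analysis to adjust for potential confounding". A baseline expectation score is a further conditional covariate, for sensitivity analyses (Control of expectation bias).

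On entry, patients must "fulfill the clinical diagnostic criteria for patellofemoral pain syndrome (PFPS), including anterior knee pain exacerbated by functional activities", and imaging must show no other knee pathology. No symptom duration is given. Prior treatment is limited by an exclusion for those who have "undergone any recent surgical procedure or targeted therapy for the patellofemoral joint"; neither the time window nor the kind of therapy is defined.

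The Data collection section names three classes of data for the database: demographics, treatment details and outcomes. Disease history is not among them.

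The Introduction states that "Patellofemoral pain syndrome (PFPS) is the most prevalent chronic knee disorder among adolescents and adults" and adds: "Evidence indicates that about 80% of individuals with PFP continue to have pain despite completing rehabilitation programs".

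**The concern.** In a preference-allocated study, nothing balances the arms except measurement and adjustment. A prognostic factor that is not recorded at baseline is difficult to recover later, and no analysis plan can adjust for it.

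Two patients with the same age, sex, BMI and baseline VAS can have very different histories: a first episode, or years of pain and a rehabilitation course that did not help. The entry criteria as printed admit both. The arms also differ visibly in burden. The control arm does one quadriceps exercise daily. The experimental arm does a multi-exercise programme with sessions of 30-60 minutes, plus CBCT, MRI, dynamic DR and gait analysis. Someone for whom simple exercise has already failed has an understandable reason to choose the second.

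If history also predicts change in pain, the VAS difference mixes treatment with case mix, and the direction is not known in advance. Recent-onset patients gathering in the lighter arm would hide a benefit; gathering in the heavier arm, they would create one.

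**Working it through.** **1. Where control could come from.**

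| Route | Symptom duration | Earlier rehabilitation of the study knee |
|---|---|---|
| Entry criteria | No limit stated | Only recent targeted therapy excluded, undefined |
| Data recorded | Not named | Not named |
| Covariates named (age, sex, BMI, baseline VAS) | Not named; list open | Not named; list open |
| Expectation score | At most an indirect proxy | At most an indirect proxy |

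No route is shown to control either variable. Only the open list leaves room for it.

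**2. Inputs for a size illustration.**
- From Sample size: standard deviation of VAS change 2.0; design difference 1.1 × 2.0 = 2.2 points; 43 per group before dropout inflation, 48 after; two-sided α = 0.05.
- Assumed, because the article gives no figures: the share of patients with long-standing or previously treated pain differs between arms by 20-30 percentage points, and such patients improve by 0.5-1.5 VAS points less.

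The printed sample-size formula gives 2 × ((1.960 + 1.645)/1.1)² = 21.5, so 22 per group, and does not reproduce 43. That is a separate matter. Here 43 serves only as the number analysed.

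**3. Bias of the unadjusted difference.**

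Standard error = 2.0 × √(2/43) = 0.431.

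Bias = difference in prevalence × prognostic effect.

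Two-sided rejection rate when there is no treatment effect = 1 − Φ(1.96 − bias/SE) + Φ(−1.96 − bias/SE).

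| Prevalence difference | Prognostic effect | Bias (VAS points) | Bias/SE | Share of 2.2 | Error rate |
|---|---|---|---|---|---|
| 0.20 | 0.5 | 0.10 | 0.23 | 5% | 5.6% |
| 0.20 | 1.0 | 0.20 | 0.46 | 9% | 7.5% |
| 0.30 | 1.0 | 0.30 | 0.70 | 14% | 10.7% |
| 0.30 | 1.5 | 0.45 | 1.04 | 20% | 18.1% |

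**4. Whether the conditional rule would catch such an imbalance.** At 48 per arm, a two-sided 5% test of two proportions has power of about 50% for 60% against 40%, and about 85% for 65% against 35%. So even if both variables were recorded and treated as part of the open list, a 20-point imbalance would go unadjusted about half the time.

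**The case against.** The strongest reply is that this is a condensed article. The covariate list is introduced as a set of examples, and the rule covers any significant imbalance. The case report forms are still to be designed, and a fuller protocol or analysis plan may name both variables. This stands in part: a reader might infer that chronicity is left uncontrolled, but the text supports only that control is not shown. What remains is that the article does describe eligibility, data recorded and covariates, and neither variable is named as recorded or adjusted for.

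A reader might also infer that earlier treatment is not limited at entry at all. That is too strong, because recent targeted patellofemoral therapy is excluded. The exclusion does leave older failed programmes eligible.

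A third tempting inference is that the 80% figure proves the confounding. It does not. It concerns pain persisting after rehabilitation, and says nothing about which arm a patient prefers or whether duration or earlier failure predicts change in VAS.

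Nor does calling the disorder chronic oblige the criteria to set a minimum duration. The diagnostic criteria are not reproduced in full, and adjustment does not need such a limit.

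Finally, the illustration is for an unadjusted comparison. Baseline VAS and expectation may carry part of the same information. That is fair, though each is brought in only after a significance test.

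**Conclusion.** The point holds as a limited recommendation that should be acted on before recruitment, which is scheduled to begin in June 2026. Under preference allocation, symptom duration and earlier rehabilitation of the study knee are plausible confounders of the primary comparison, and the article does not show that either will be recorded or adjusted for.

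The size is illustrative: a bias of 0.1-0.45 VAS points, about 5-20% of the 2.2-point design difference, and an error rate of about 6-18% instead of 5%. Both driving inputs are assumptions, and the calculation gives no credit to the covariates already named. With no prognostic effect, or no difference between arms, the bias is zero. The figures show that a moderate imbalance could matter; they do not show that it will occur.

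**What to change.** Add two baseline fields to the case report form: duration of symptoms in the study knee, and earlier rehabilitation of that knee. In the Statistical analysis section, pre-specify both, together with age, sex, BMI and baseline VAS, as covariates in the primary VAS model, entered whatever the baseline significance tests show.

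The cost is two fields, one sentence and two more model terms. If each covariate takes one term, the model has eight parameters (intercept, arm and six covariates), which leaves 86 − 8 = 78 residual degrees of freedom with 86 patients analysed. No change to eligibility is needed for this purpose.

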**Methods and analysis:**

This single-centre, prospective, interventional cohort study will investigate the effectiveness of a biomechanically monitored targeted exercise protocol combined with Traditional Chinese Medicine (TCM) compared with conventional exercise combined with TCM in patients with patellofemoral pain syndrome (PFPS). We will consecutively recruit 96 eligible patients. Participants will be assigned to either an experimental group or a control group based on their preference after receiving standardized information. The experimental group will receive biomechanical monitoring, targeted exercise, and Traditional Chinese Medicine (TCM), whereas the control group will receive conventional exercise and the same TCM regimen.

Outcomes will be assessed at baseline, 6 weeks, 6 months and 3 years post-intervention. The primary outcome measure will be pain intensity measured using the Visual Analog Scale (VAS). Secondary outcome measures will include: biomechanical parameters; pain (Knee Pain Scale); joint function (Lysholm Knee Scoring Scale); kinetic parameters (mean power and pulling acceleration during stair climbing using the IDEEA system); spatiotemporal gait parameters (walking speed, step frequency, double support time during stair climbing using IDEEA); and quality of life (36-Item Short Form Health Survey).

For statistical analysis, independent samples *t*-tests will be used for between-group comparisons, and linear mixed-effects models will be applied for outcomes measured at multiple time points. To control for expectation bias, patients' treatment expectation scores will be recorded at baseline and adjusted as covariates if significant between-group differences exist. Baseline characteristics will be compared, and any imbalanced variables will be included as covariates in the primary analysis. A two-tailed *P*-value < 0.05 will be considered statistically significant.

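### Patients choose their group, but the primary analysis adjusts for confounders only if a baseline significance test flags them, and that test often misses small to moderate imbalances

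*Protocol article*

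**What the plan says.** Section 2.5 of the protocol article lets patients choose: "Patients will be assigned to either the experimental group or the control group based on their preference". Section 3.2.2 recognises the consequence: "As this is a non-randomized study, baseline characteristics (including age, sex, body mass index, and baseline VAS score) will be compared between groups". For the 6-week primary outcome, "an independent samples *t*-test will be used to compare the change scores between the two groups". Covariates come in under a condition: "if any significant imbalance is detected, these variables will be included as covariates in the primary analysis to adjust for potential confounding". No separate threshold is given for the baseline comparison; the general one is "A two-tailed *P*-value < 0.05 will be considered statistically significant for all analyses".

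The Abstract words the rule differently: "any imbalanced variables will be included as covariates in the primary analysis". That points to the flagged variables only. Section 3.2.2 names four variables and can be read as bringing in all of them once any one is flagged.

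The baseline expectation score (section 3.1.3) is also used only if it differs significantly between groups, and then only in sensitivity analyses. The Abstract has the same condition without that limit. No other control of confounding is stated for the primary comparison.

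**The concern.** When patients choose their treatment, baseline differences are expected, so testing whether they are zero does not answer a useful question. A baseline P-value depends on the sample size as well as on the size of the imbalance, and it carries no information on whether the variable predicts VAS change. A prognostic variable can miss the threshold and stay out of the model.

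Baseline VAS is the clearest candidate, because it is part of the change score. An independent-samples t-test has no place for covariates, so the form of the primary model also depends on the baseline results. At stake is whether the primary between-group difference carries confounding from variables that the trial already records.

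**Working it through.** **Inputs.** From the document: 48 per group planned, 43 per group before the dropout allowance, two-sided 0.05, σ = 2.0 and an assumed difference of 1.1σ = 2.2 VAS points (section 2.6). Assumptions, because the document gives no figures: size of the true imbalance (d, in SD units) and correlation of each covariate with VAS change (ρ).

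The plan states no figure for the adjustment rule itself. Its dropout step reproduces: 86/0.90 = 95.6, so 96. Its 43 per group does not follow from the printed formula, since 2 × ((1.960 + 1.645)/1.1)² = 21.5. That is a separate matter, and the planned group sizes are taken as given here.

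**Step 1: how often the gate opens.** The noncentrality is d × √(n/2), and the power comes from the noncentral t with 2n − 2 degrees of freedom. For d = 0.3 and n = 48 it is 0.3 × √24 = 1.47. The normal approximation gives Φ(1.47 − 1.96) = 31%, and the exact value is 30.7%.

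| True imbalance (SD) | 48 per group | 43 per group |
|---|---|---|
| 0.2 | 16% | 15% |
| 0.3 | 31% | 28% |
| 0.4 | 49% | 45% |
| 0.5 | 68% | 63% |
| 0.8 | 97% | 96% |

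The even-odds point is 1.96 × √(2/48) = 0.40 SD. Preference allocation need not give equal groups; with a 64/32 split, the chance at 0.3 SD is 28%. For sex, 50% against 65% is flagged 32% of the time.

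**Step 2: one confounder, no treatment effect, 48 per group (20,000 simulated trials).** Unadjusted bias is d × ρ × σ. At d = 0.3 this is 0.3 × 0.3 × 2.0 = 0.18 points for ρ = 0.3, and 0.3 × 0.5 × 2.0 = 0.30 for ρ = 0.5. The second value is plausible for baseline VAS: with equal variances and a baseline to follow-up correlation of 0.5 (both assumed), baseline correlates −0.5 with change.

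Under the gate, bias comes from the trials not flagged, 1 − 0.305 = 0.695 of them. Their mean bias is 0.120 (ρ = 0.3) or 0.196 (ρ = 0.5), which gives 0.695 × 0.120 = 0.083 and 0.695 × 0.196 = 0.136. The simulated values are 0.085 and 0.135, with type I error of 5.3% and 5.5%. Always adjusting leaves 0.003 points or less, and 4.8-4.9%.

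**Step 3: four independent confounders, all in the same direction, d = 0.3 and ρ = 0.3 each.** Unadjusted bias is 4 × 0.18 = 0.72 points. At least one is flagged with probability 1 − (1 − 0.307)⁴ = 77%.

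| Rule | Bias, type I error (48 per group) | Bias, type I error (43 per group) |
|---|---|---|
| No adjustment | 0.72, 41% | 0.73, 39% |
| Flagged variables only | 0.33, 11.8% | 0.35, 11-12% |
| All four once any is flagged | 0.11, 8.1% | about 0.14, 8% |
| Always adjust | 0.00, 5.0% | 0.0, 5% |

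**Step 4: sensitivity of step 3 (43 per group, flagged only).** With ρ = 0.2 each: 0.23 points and 8.3%. With ρ = 0.1 each: 0.12 points and 5.9%. With two imbalances in each direction at ρ = 0.3: 0.0 points and 4%.

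**The case against.** A reader might infer that most real imbalances stay uncorrected, that the primary t-test is therefore biased, and that its P-value is too small. The documents do not support that. The test misses more than half only below about 0.4 SD; at 0.5 SD about two thirds are flagged and at 0.8 SD nearly all. The document gives neither the size of the imbalances nor their prognostic strength. Bias needs both, and it can run towards the null as well as away from it.

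The four-confounder case is close to a worst case. It needs every covariate imbalanced in the same direction, and four correlations of 0.3 together explain 4 × 0.09 = 36% of the variance in VAS change. Even then, 0.35 points is 16% of the assumed 2.2. The more literal reading of section 3.2.2 roughly halves the damage or better.

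Further fair points:
- The trigger is stated in advance and uses baseline data only, and naming the adjusted model may be left to an SAP.
- The covariate list is introduced as non-exhaustive, so TCM syndrome type is unnamed rather than excluded.
- Adjustment need not improve precision: at ρ = 0.1 each, the simulated standard error rose from 0.430 to 0.451.
- Under self-selection, ANCOVA and change-score analyses rest on different assumptions.
- The clean result for fixed adjustment comes from simulations in which all confounders are measured and act linearly.

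These points limit the size of the problem. They do not defend the rule: it is written into the protocol, its trigger does not measure confounding, and its two statements can lead to different primary estimates.

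**Conclusion.** The concern holds in a limited form. Adjustment is the only stated control of confounding for the primary comparison, and it depends on a test with about 16-49% power for imbalances of 0.2-0.4 SD at 48 per group. Confounding of that size will often go uncorrected.

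The consequence is conditional on the missed variables predicting VAS change. It is small for a single confounder: about 0.1 points at 0.3 SD, or 4-6% of the assumed 2.2 (0.085/2.2 and 0.135/2.2), with type I error of 5-6%. It becomes material only if several confounders act together: up to about 0.35 points and 11-12% under the flagged-only reading, or about 0.14 points and 8% if all variables enter together. The power figures follow from the planned group size and the 5% threshold. The bias figures rest on assumed imbalances and correlations.

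**What to change.** In section 3.2.2 and the Abstract, replace the t-test and the conditional rule with one pre-specified primary model: ANCOVA of 6-week VAS on group, baseline VAS, age, sex, BMI and baseline expectation score, fitted whatever the baseline P-values. Consider TCM syndrome type as a further covariate; it has to be determined anyway to select the TCM regimen. Bring section 3.1.3 into line, so that the expectation score is no longer gated or confined to sensitivity analyses. Describe baseline balance by standardised differences, and keep the unadjusted t-test as a supportive analysis. This also removes the difference between the two statements of the rule.

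The cost is rewording and up to six degrees of freedom: with 86 analysed, 84 residual degrees of freedom become 78. The standard error may rise slightly if the covariates are weakly prognostic. Unmeasured confounding remains and should be stated as a limitation. Enrolment is scheduled for June 2026, so the change should be made before any data are collected.
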